**ETHICAL COMMITTEE:**

Fundación para la investigación biosanitaria del Hospital Gregorio Marañón  
Institutional Review Board, FIBHGM-ECNC003-2010 (FIBHGM-10-01).

## **BACKGROUND**

Critically-ill pediatric patients frequently require endotracheal intubation. Post-extubation upper airway obstruction (UAO) is a common complication that affects up to a third of patients who require endotracheal intubation [1–3].

Laryngeal edema is more frequent and severe in children than in adults due to the small diameter of their airways. Indeed, this type of edema in children affects the subglottal region more frequently than the glottal region [2,4]. Signs of airway obstruction include stridor and respiratory distress, which require reintubation in 6-13% of patients [1–3].

Risk factors related to post-extubation UAO include underlying respiratory or neurological disease, prolonged intubation (more than 36-48h), reintubation, a young age ( $\leq 24$  months of age), or infants weight less than 5 kilograms [1,2].

The obstruction of the upper airways has significant effects on the evolution of the patient. This complication may increase morbidity and mortality, length of hospital stay, duration of mechanical ventilation and healthcare-related costs, especially when the patient requires reintubation [1,2,5,6].

Steroids are one of the most widely used therapies for post-extubation UAO, as they have anti-inflammatory effects, thereby reducing the risk for laryngeal edema and airway obstruction. A range of steroids such as hydrocortisone, methylprednisolone and dexamethasone have been used for the prevention and management of post-extubation UAO [4,7]. Contradictory results have been obtained in studies assessing the effectiveness of steroids in preventing post-extubation UAO [5–10].

## EFFECTIVENESS OF STEROIDS IN PREVENTING UPPER AIRWAY OBSTRUCTION AFTER EXTUBATION IN CRITICALLY-ILL CHILDREN.

A recent meta-analysis [7] of studies in adult patients with and without UAO risk factors receiving different regimens of steroids showed that steroids reduce the incidence of upper airway complications and reintubation in high-risk patients.

Studies in pediatric patients are based on widely heterogeneous samples of patients, doses and timing of prophylactic therapy ranging from one hour to 24 hours prior to extubation [4,7].

In studies on the use of dexamethasone in children, a variety of regimens have been used versus placebo. Some authors report a decrease in the incidence of stridor [5,8], whereas two studies show a reduction in the incidence of reintubation [8,9]. A study in neonates concluded that dexamethasone reduced the risk for reintubation [10]. In contrast, this benefit has not been proven in other studies in children [11] and neonates [12].

Baranwal et al [3] compared two regimens in high-risk pediatric patients: starting dexamethasone therapy 6 hours vs 24 hours before extubation. The authors found that the 24-h regimen reduced significantly the incidence of UAO, as compared to the 6-h regimen.

A Cochrane's systematic review [4] concluded that the effectiveness of steroids in preventing UAO in children has not been sufficiently demonstrated, and further studies are needed to assess its potential benefits, especially in high-risk patients.

In light of the lack of consistent evidence, we have designed a randomized study to compare the effectiveness of dexamethasone vs placebo in the prevention of post-extubation UAO in high-risk pediatric patients (> 48 hours intubated).

The main objective of this study is to explore whether dexamethasone is effective in preventing and reducing the severity of UAO symptoms in critically-ill children vs. placebo. Secondary objectives include investigating whether dexamethasone reduces the incidence of reintubation and evaluating the potential secondary effects associated with this medication.

## **METHODS**

### **STUDY DESIGN**

This is a multicentric, prospective, double-blind, randomized, placebo-controlled, phase IV clinical trial. Five pediatric intensive care units of hospitals located in Spain will participate in the study. The study protocol was developed in accordance with the Standard Protocol Items: Recommendations for Interventional Trials (SPIRIT) checklist.

### **ETHICS APPROVAL AND CONSENT TO PARTICIPATE**

This study protocol was designed in accordance with the Declaration of Helsinki (1964) and subsequent versions. The final version of this study protocol was approved by Ethics Committee of Gregorio Marañón Hospital, Madrid, Spain (IBHGM-ECNC003-2010) and the local Ethics Committee of all participating centers. The Principal Investigator will ensure that the study is performed in accordance with laws and regulations governing the performance of clinical trials and will communicate protocol modifications to relevant parties.

|                                                                                                                      |
|----------------------------------------------------------------------------------------------------------------------|
| EFFECTIVENESS OF STEROIDS IN PREVENTING UPPER AIRWAY OBSTRUCTION AFTER EXTUBATION IN CRITICALLY-ILL CHILDREN. |
|----------------------------------------------------------------------------------------------------------------------|

The rationale for using placebo is that the effectiveness of steroids has not been confirmed to date, and other medications have not been proven to be effective in preventing post-extubation complications.

The study investigator responsible for patient recruitment in each center will provide oral and written information on the study to the patients or their legal representatives when their age or clinical state prevents them from giving consent. Written informed consent will be required prior to inclusion.

The local Ethics Committees will be given access to original records and databases.

## **STUDY POPULATION**

The sample will include children between 1 month and 16 years of age admitted to the ICU who require intubation for more than 48 hours, regardless of their condition. Patients with airway malformations, suspected or confirmed croup syndrome, tracheitis or epiglottitis and those who had previously underwent any surgery involving upper or lower airway will be excluded. Furthermore, other exclusion criteria were the administration of steroid therapy within the last seven days, patients who had a previous extubation failure during the stay or refusal to participate in the study.

## **RECRUITMENT**

Study candidates will be identified by a study physician, who will explain the study to parents or guardians. Written informed consent will be obtained from

# EFFECTIVENESS OF STEROIDS IN PREVENTING UPPER AIRWAY OBSTRUCTION AFTER EXTUBATION IN CRITICALLY-ILL CHILDREN.

parents or guardians prior to inclusion in the study. CONSORT (*Consolidated Standards of Reporting Trials*) flow diagram is shown in Figure 1.

Figure 1 CONSORT Flow Diagram

[figure not shown]

## RANDOMIZATION AND MASKING

Patients will be assigned to one of the two therapy groups on a 1:1 ratio by simple randomization using a randomization table on EPIDAT 3.1 (Epidat: software package for epidemiological data analysis. 2006. Consellería de Sanidade, Xunta de Galicia, España; Organización Panamericana de la Salud; Universidad CES, Colombia). The Coordinating Center will send a table for

Protocol number: FIBHGM-ECNC003-2010(FIBHGM-10-01)

|                                                                                                               |
|---------------------------------------------------------------------------------------------------------------|
| EFFECTIVENESS OF STEROIDS IN PREVENTING UPPER AIRWAY OBSTRUCTION AFTER EXTUBATION IN CRITICALLY-ILL CHILDREN. |
|---------------------------------------------------------------------------------------------------------------|

sequential randomization of patients. This table will contain the number of medication that has been assigned to each patient. The treatment group will not be detailed in the randomization table. This table will also include a number of reserve medication for use in case of deterioration, loss, or if the drug is rendered unusable. The Pharmacy Unit of the Coordinating Center will send treatment-arm assignments labeled and blinded as established in the randomization table for each center.

The labeling and blinding of medication kits will be performed by the Pharmacy Unit of the Coordinating Center, which will keep an open record of these kits and their composition. This record will be coded and stored by the pharmacist of the Coordinating Center responsible for the labeling and submission of samples.

In case of severe or unexpected adverse events related to the medication, the Principal Investigator will require the responsible pharmacist to unblind the codes identifying the sample. The Principal Investigator will be informed so that timely action can be taken. The unblinding of any code will be recorded by the pharmacist responsible for sample blinding.

## **INTERVENTION**

The treatment group will receive intravenous 0.25 mg/kg/dose (to a maximum of 8 mg) every 6 hours, for a total of 4 doses. The first dose will be administered between 6 and 12 hours prior to extubation. The placebo group will be administered saline 0.9%. The study medication will have the same aspect and characteristics than placebo and both will be administered in the same way.

|                                                                                                                      |
|----------------------------------------------------------------------------------------------------------------------|
| EFFECTIVENESS OF STEROIDS IN PREVENTING UPPER AIRWAY OBSTRUCTION AFTER EXTUBATION IN CRITICALLY-ILL CHILDREN. |
|----------------------------------------------------------------------------------------------------------------------|

Dose adjustment, discontinuance or reinitiation of treatment will not be allowed. Inspections will be performed to ensure that the treatment is being administered adequately.

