### **DATA COLLECTION AND ASSESSMENT OF EFFICACY**

On inclusion, demographic (age, sex and weight) and clinical data will be collected, as follows:

- Diagnosis (six diagnostic groups will be established): surgery, lower airway obstruction, neurological disease, sepsis, trauma and other diagnosis.
- Assessment of severity: the clinical status of the patient will be assessed using PIM2, PRIMS 3 and PELOD scores prior to extubation.
- Size and type of endotracheal tube (cuffed or uncuffed).
- Route of intubation (oral, nasal).
- Previous need for endotracheal tube replacement.
- Previous airway endoscopies.
- Respiratory infection confirmed by endotracheal aspirate culture.
- Presence of blood in endotracheal aspirate.
- Duration of endotracheal intubation prior to extubation (days).

The primary endpoint is the reduction of the incidence of moderate to severe UAO symptoms within 48 hours after extubation. Moderate-severe UAO symptoms will be considered if stridor or Taussig score >5 are present. The secondary endpoints are the presence of reintubation and the potential secondary effects associated with dexamethasone.

|                                                                                                               |
|---------------------------------------------------------------------------------------------------------------|
| EFFECTIVENESS OF STEROIDS IN PREVENTING UPPER AIRWAY OBSTRUCTION AFTER EXTUBATION IN CRITICALLY-ILL CHILDREN. |
|---------------------------------------------------------------------------------------------------------------|

A record of the following variables will be kept at 15 minutes, 1h, 2h, 6h, 12h, 24h and 48 hours after extubation:

1. UAO Taussig score[13], a clinical scoring system for the assessment of UAO severity; evaluating stridor, retractions, inflow of air into the lungs, cyanosis and consciousness (table 1). Presence of inspiratory stridor.
2. Need for and frequency of additional therapies for respiratory distress: adrenaline or nebulized budesonide, intravenous steroids, heliox or non-invasive ventilation.
3. Hemodynamic (blood pressure, heart rate) and respiratory (peripheral oxygen saturation, respiratory rate) parameters.
4. Arterial pCO2 and pO2 and glycemia. Blood samples will not be routinely collected, they will be drawn only for clinical purpose.
5. Need for reintubation, time point and cause.
6. Presence of digestive bleeding.
7. Occurrence of infection.

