The timing of parameter recording is shown in Table 2.

All interventions that patients require for their treatment are allowed but those that could affect the upper airway (respiratory tract infections, reintubations, etc.), will be recorded and will be taken into account in the statistical analysis

A co-investigator will be appointed as responsible for each participating center in order to verify the correct adherence to the study protocol, checking in every 8 hour shift that the medication is prescribed in the treatment and that it has been administered. This investigator will also be responsible of complete follow up of every patient.

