## **EVALUATION OF SAFETY**

The occurrence of adverse events from inclusion to study completion will be recorded for all patients. All patients will be monitored until hospital discharge, including those who discontinue their participation in the study. Severe adverse events during hospital stay will be reported to the Study Coordinator and Promotor. In case of occurrence of severe adverse events, follow-up will be performed until remission or until a diagnosis is made and its association with the study medication is established.

A severe adverse event is defined as any adverse event that the patient's treating physician considers to require treatment on the basis of the characteristics and clinical status of the patient. Severe hyperglycemia is any glycemia > 200 mg/dl that persists for more than 6 hours and/or physicians consider to require treatment on the basis of the clinical status of the patient.

Any unused medication will be disposed in accordance with the protocol established by the Pharmacy Unit in collaboration with the Unit of Environmental Management of the Coordinating center, in compliance with ISO 14.001. Upon study completion, any unused or partially used medication will be sent back to the Coordinating Center.

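### The ban on stopping study drug carries no safety exception, and no other section of the protocol supplies one for an individual child

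*Protocol*

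**What the plan says.** The Intervention section of the protocol sets a fixed course: 0.25 mg/kg per dose (maximum 8 mg), four doses at 6-hour intervals, with the first dose 6 to 12 hours before extubation. It then states: "Dose adjustment, discontinuance or reinitiation of treatment will not be allowed". The next sentence provides for inspections of administration. Under Data Collection and Assessment of Efficacy, a co-investigator at each centre checks every 8-hour shift that the medication was prescribed and given.

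Four other statements bear on a child who has a drug-related event during the course:

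- Randomization and Masking: "In case of severe or unexpected adverse events related to the medication", the pharmacist is asked to break the code. It continues: "The Principal Investigator will be informed so that timely action can be taken". The action is not named.
- Data Collection and Assessment of Efficacy: "All interventions that patients require for their treatment are allowed".
- Evaluation of Safety: an adverse event is severe if the "treating physician considers to require treatment on the basis of the characteristics and clinical status of the patient". There is also a specific definition: "Severe hyperglycemia is any glycemia > 200 mg/dl that persists for more than 6 hours", and/or that the physician considers to need treatment.
- Evaluation of Safety, on follow-up: "All patients will be monitored until hospital discharge, including those who discontinue their participation in the study".

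**The concern.** The ban names discontinuance and is unconditional. Once a child has a severe event attributed to study drug and the code has been broken, withholding the remaining doses is an obvious step to consider. Followed literally, the protocol lets the site treat the event but not stop the drug suspected of causing it. A clinician who withholds a dose would be recorded as departing from protocol by the shift checks, with no protocol text in support.

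If the authors meant only to forbid elective changes to a short fixed course, the text does not say so. Each of the five centres must then decide for itself when it may depart from an explicit prohibition. The participants are critically ill children, often enrolled on a parent's or guardian's consent. This is not detail that can be left to an analysis plan: when dosing may stop is a protocol rule, and the protocol states it too broadly.

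**Working it through.** **Is there an exception anywhere?** The sections that could supply one, set against the ban:

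| Section | What it covers | Lets one child's doses be withheld for safety? |
|---|---|---|
| Ethics Approval and Consent | General commitment to the Declaration of Helsinki and to clinical trial law | No rule stated |
| Randomization and Masking | Code break after a severe or unexpected drug-related event | Action not specified |
| Data Collection and Assessment of Efficacy | Treatments that patients need are allowed | Covers treating the event; silent on study drug |
| Evaluation of Safety | Recording, reporting, follow-up; foresees patients leaving the study | No dosing rule |
| Data Processing and Auditing | Stopping the whole trial for excess harm on steroid | Trial level only |

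None does.

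**How many doses could be at issue?** Doses fall at 0, 6, 12 and 18 h. With extubation 6 to 12 h after the first dose, the last dose falls 18 − 12 = 6 h to 18 − 6 = 12 h after extubation. All counts below are upper bounds.

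*Event the physician judges to need treatment.* Straight after dose 1, 2, 3 or 4, there remain 3, 2, 1 or 0 doses. Three doses are 3 × 0.25 = 0.75 mg/kg, at most 3 × 8 = 24 mg.

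*Hyperglycemia under the persistence criterion.* With onset at t hours after the first dose and a recognition delay of d hours, the event is recognised just after t + 6 + d, and the doses later than that remain. The delay matters because, on glycemia and blood gases, the protocol says: "Blood samples will not be routinely collected, they will be drawn only for clinical purpose".

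| Delay d | 2 doses remain | 1 dose remains | 0 remain |
|---|---|---|---|
| 0 h | t from 0 to under 6 h | 6 to under 12 h | from 12 h |
| 3 h | 0 to under 3 h | 3 to under 9 h | from 9 h |
| 6 h | none | 0 to under 6 h | from 6 h |
| 12 h | none | none | all |

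The maximum here is 2 doses: 0.5 mg/kg, at most 16 mg.

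**What would permitting safety stops cost?** This prices the remedy; it is not evidence of the defect. First, the plan's own sample size. With h = 0.4, n = 2 × ((1.960 + 0.842)/0.4)² = 98.1, so 99 per arm, and 99/0.9 = 110. The stated 110 reproduces and already includes the 10% loss, so 99 per arm is the relevant baseline.

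For power, take the unrounded h = 2·asin(√0.33) − 2·asin(√0.16) = 0.401 and power = Φ(h·√(n₁n₂/(n₁+n₂)) − 1.96). The stop rates are assumptions, applied to one arm only, with the stopped children leaving the per-protocol set:

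| Assumed stops in one arm | n₁ / n₂ | Per-protocol power |
|---|---|---|
| 0 | 99 / 99 | 80.5% |
| 2% (2 children) | 99 / 97 | 80.1% |
| 5% (5 children) | 99 / 94 | 79.5% |
| 10% (10 children) | 99 / 89 | 78.4% |

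This counts lost numbers only, not bias.

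**The case against.** A reader might infer that the ban flatly contradicts the unblinding procedure. The documents do not support that. The masking section never mentions withholding doses; timely action can mean treating the event, which the protocol allows. Both sentences can be obeyed together, so the tension is practical, not textual.

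Context also favours a narrower intent. Discontinuance is listed between dose adjustment and reinitiation and is followed at once by inspections, so the sentence reads as an adherence rule for a fixed course. Evaluation of Safety expects some patients to leave the study, so the authors probably did not mean every child to finish whatever happens. The ethics section adds a general safeguard.

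The worked example is modest too: hyperglycemia is treatable, few doses remain, no event rate is given, and divergent practice between centres is a possibility, not a demonstrated fact.

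Much of this stands. It shows that the literal reading was probably not intended. It does not supply the exception: leaving the study is not a safety stop of the drug, a general ethical commitment states no dosing rule, and permission to treat does not plainly extend to overriding a specific prohibition that is checked every shift.

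**Conclusion.** The point holds as an over-broad rule of unclear scope. It is worth correcting because, applied as written, the rule would keep dosing a child with a severe drug-related event. At most 3 doses are at issue after an event that the physician judges to need treatment, and at most 2 under the hyperglycemia persistence criterion, falling to 0 if recognition is 12 h late. These bounds assume doses given exactly on schedule.

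Nothing here shows that any child would in fact be denied a safety stop, or how many might face the question. The endpoint, the sample size and the planned analyses are unaffected by the defect itself.

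**What to change.** Amend the sentence in the Intervention section so that:

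- dose adjustment, elective discontinuance and reinitiation are not allowed;
- the investigator may permanently withhold remaining doses when continuing is judged unsafe, for example after a severe or unexpected event judged related to study medication;
- dosing stops if participation is withdrawn;
- children whose dosing stops continue the 48 h assessments where consent allows and stay in their randomised arm for the intention-to-treat analysis.

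The safety stop should be discretionary. The protocol's definition of a severe event takes in anything the physician considers to need treatment, so a mandatory stop would end courses for readily controlled events.

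The wording costs one clause; follow-up to discharge and an intention-to-treat analysis are already planned. The downside is some incomplete courses, possibly more on dexamethasone. The loss of per-protocol power is small under the assumed rates, but unequal stopping could bias that comparison, so the intention-to-treat result should be read beside it.

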### **DATA COLLECTION AND ASSESSMENT OF EFFICACY**

On inclusion, demographic (age, sex and weight) and clinical data will be collected, as follows:

- Diagnosis (six diagnostic groups will be established): surgery, lower airway obstruction, neurological disease, sepsis, trauma and other diagnosis.
- Assessment of severity: the clinical status of the patient will be assessed using PIM2, PRIMS 3 and PELOD scores prior to extubation.
- Size and type of endotracheal tube (cuffed or uncuffed).
- Route of intubation (oral, nasal).
- Previous need for endotracheal tube replacement.
- Previous airway endoscopies.
- Respiratory infection confirmed by endotracheal aspirate culture.
- Presence of blood in endotracheal aspirate.
- Duration of endotracheal intubation prior to extubation (days).

The primary endpoint is the reduction of the incidence of moderate to severe UAO symptoms within 48 hours after extubation. Moderate-severe UAO symptoms will be considered if stridor or Taussig score >5 are present. The secondary endpoints are the presence of reintubation and the potential secondary effects associated with dexamethasone.

|                                                                                                               |
|---------------------------------------------------------------------------------------------------------------|
| EFFECTIVENESS OF STEROIDS IN PREVENTING UPPER AIRWAY OBSTRUCTION AFTER EXTUBATION IN CRITICALLY-ILL CHILDREN. |
|---------------------------------------------------------------------------------------------------------------|

A record of the following variables will be kept at 15 minutes, 1h, 2h, 6h, 12h, 24h and 48 hours after extubation:

1. UAO Taussig score[13], a clinical scoring system for the assessment of UAO severity; evaluating stridor, retractions, inflow of air into the lungs, cyanosis and consciousness (table 1). Presence of inspiratory stridor.
2. Need for and frequency of additional therapies for respiratory distress: adrenaline or nebulized budesonide, intravenous steroids, heliox or non-invasive ventilation.
3. Hemodynamic (blood pressure, heart rate) and respiratory (peripheral oxygen saturation, respiratory rate) parameters.
4. Arterial pCO2 and pO2 and glycemia. Blood samples will not be routinely collected, they will be drawn only for clinical purpose.
5. Need for reintubation, time point and cause.
6. Presence of digestive bleeding.
7. Occurrence of infection.

The timing of parameter recording is shown in Table 2.

All interventions that patients require for their treatment are allowed but those that could affect the upper airway (respiratory tract infections, reintubations, etc.), will be recorded and will be taken into account in the statistical analysis

A co-investigator will be appointed as responsible for each participating center in order to verify the correct adherence to the study protocol, checking in every 8 hour shift that the medication is prescribed in the treatment and that it has been administered. This investigator will also be responsible of complete follow up of every patient.

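### Glycaemia is recorded only after extubation and only from clinically drawn samples, so the baseline and the first 6 to 12 hours of exposure are not captured for a stated secondary endpoint

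*Protocol*

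**What the plan says.** The closing paragraph of the introductory text gives a secondary objective of "evaluating the potential secondary effects associated with this medication". The section on data collection and assessment of efficacy repeats it as an endpoint: "The secondary endpoints are the presence of reintubation and the potential secondary effects associated with dexamethasone".

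The same section sets the recording times: "A record of the following variables will be kept at 15 minutes, 1h, 2h, 6h, 12h, 24h and 48 hours after extubation". Glycaemia shares item 4 of that list with arterial pCO2 and pO2, and the item ends with the rule "Blood samples will not be routinely collected, they will be drawn only for clinical purpose". Digestive bleeding and infection are items 6 and 7. The list of data collected on inclusion has no glucose value, and Table 2 has no glycaemia row.

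Under Intervention, the drug is given "every 6 hours, for a total of 4 doses", and "The first dose will be administered between 6 and 12 hours prior to extubation".

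Under Evaluation of Safety, adverse events are recorded for all patients from inclusion, with monitoring to hospital discharge. Table 2 marks adverse event assessment at the visit before extubation and at visits 2 to 8. The same section states: "Severe hyperglycemia is any glycemia > 200 mg/dl that persists for more than 6 hours", and adds, joined by and/or, a second route by which the physician judges that treatment is required.

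**The concern.** Three features combine.

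- **Timing.** Exposure begins hours before the first scheduled glycaemia record, and there is no pre-dose value against which to judge a later one.
- **Sampling.** Whether a child has any value depends on clinical need after randomisation. Because glycaemia is listed with the blood gases, it is reasonable to suppose that a child in respiratory distress is more likely to be sampled. The trial expects fewer such children on dexamethasone.
- **Definition.** Persistence above 200 mg/dl for more than 6 hours can be shown only in a child measured more than once.

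At stake is how a finding of no excess hyperglycaemia could be read. With the data as planned, it could not be told apart from not having looked during early exposure, or from having looked less often in one arm. This is not a matter that an analysis plan can repair later: values never entered in the data log cannot be analysed.

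**Working it through.** **1. Exposure before the first scheduled record.** Four doses at 6-hour intervals fall at 0, 6, 12 and 18 h, a span of 3 × 6 = 18 h. Relative to extubation:

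- First dose 6 h before: doses at -6, 0, +6, +12 h.
- First dose 12 h before: doses at -12, -6, 0, +6 h.

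The part of the span before extubation is 6/18 = 33% to 12/18 = 67%. The first record, at +0.25 h, comes 6.25 to 12.25 h after the first dose. The later part is well covered: the 48 h window runs 48 - 12 = 36 h to 48 - 6 = 42 h past the last dose.

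**2. Persistence on the planned grid.** The times are 0.25, 1, 2, 6, 12, 24 and 48 h. The longest gap available by 6 h is 6 - 0.25 = 5.75 h, which is not more than 6 h. Even with a sample at every time, persistence can first be shown at the 12 h record. With clinical samples only, it can be assessed only in children who happen to have suitably spaced values.

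**3. Effect of sampling linked to UAO (illustration).** The UAO proportions, 0.33 on placebo and 0.16 on dexamethasone, come from the Sample Size section. The documents give no hyperglycaemia or sampling rates, so these are assumed:

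- True hyperglycaemia is 10% on placebo and 20% on dexamethasone, a risk ratio of 2.0.
- A child has a usable value with probability s1 if UAO occurs and s0 if not.
- Hyperglycaemia is independent of UAO within an arm.
- Unsampled children count as event-free.

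Proportion sampled:

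- Placebo = 0.33·s1 + 0.67·s0
- Dexamethasone = 0.16·s1 + 0.84·s0

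Recorded risk ratio = 2.0 × (dexamethasone sampled / placebo sampled). For s1 = 0.9 and s0 = 0.4, placebo is 0.297 + 0.268 = 0.565, dexamethasone is 0.144 + 0.336 = 0.480, and the ratio is 2.0 × 0.480/0.565 = 1.70.

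| s1 / s0 | Placebo sampled | Dexamethasone sampled | Recorded ratio (true 2.0) | Recorded ratio (true 1.0) |
|---|---|---|---|---|
| 0.9 / 0.8 | 0.833 | 0.816 | 1.96 | 0.98 |
| 0.9 / 0.5 | 0.632 | 0.564 | 1.78 | 0.89 |
| 0.9 / 0.4 | 0.565 | 0.480 | 1.70 | 0.85 |
| 0.9 / 0.3 | 0.498 | 0.396 | 1.59 | 0.80 |
| 0.8 / 0.2 | 0.398 | 0.296 | 1.49 | 0.74 |
| 0.5 / 0.5 | 0.500 | 0.500 | 2.00 | 1.00 |

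**4. Effect on power (same assumptions).** With 110 × 0.9 = 99 children per arm and a two-sided 5% z-test, power is 50% if every child is sampled. It is 40% at 0.9/0.8 and 13% at 0.9/0.3. At 0.5/0.5 the ratio is unbiased but power is 27%.

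**5. Role of the denominator.** If only sampled children are counted, the same model gives 20% against 10%, a ratio of 2.0. The dilution in step 3 therefore comes from the denominator, and the protocol does not say which one it will use. The sampled-only ratio is unbiased only while hyperglycaemia is independent of UAO within an arm. Rescue intravenous steroids or adrenaline could break that independence.

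**The case against.** The strongest reply is that safety is already collected broadly. Adverse events are recorded from inclusion and followed to discharge, Table 2 marks them before extubation, and digestive bleeding and infection need no blood draw. This stands. A reader might infer that the whole side-effect objective is measured only after extubation and only when blood is drawn. The documents do not support that, and the point is confined to glycaemia.

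Second, severe hyperglycaemia can also qualify through the physician's judgement that treatment is needed, with no second value. A child who is noticed and treated at any time from inclusion would therefore count. This stands too, and it weakens any argument that the stopping rule under Data Processing and Auditing is undermined, because severe adverse events are themselves defined by judged need for treatment. It does not close the gap: a treatment decision presupposes a known value, and unsampled or untreated hyperglycaemia is invisible by either route.

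Third, the diluted ratios rest on assumed rates and on counting unsampled children as event-free, which no section states. That is right. The choice of denominator may properly be left to an analysis plan. The collection window may not, because the protocol fixes it.

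Fourth, avoiding research blood draws in critically ill children is a legitimate choice, and rescue therapies are already recorded at every time point. Both are accepted, and the fix works within them.

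**Conclusion.** The point holds for glycaemia. As written, the plan collects no baseline value and no glycaemia data for the first 6 to 12 hours of exposure (33-67% of the dosing span). It also sets a persistence criterion that cannot be applied evenly to all children. This much follows from the protocol text and needs no assumption.

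A reader might go further and infer that the design hides hyperglycaemia on dexamethasone. The documents do not support that. It requires that UAO prompts sampling, that dexamethasone lowers UAO, and that unsampled children are counted as event-free. None of these is established: the first and third are not stated, and the second is the trial's hypothesis. Even with all three, the signal is diluted (2.0 becomes 1.49 to 1.96 over the assumed range) and not removed. If sampling is unrelated to UAO, or UAO does not differ between arms, the ratio is unbiased and only power is lost. The real size is unknown. The primary endpoint and the sample size are not affected.

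**What to change.** No new blood draw and no change to treatment are needed.

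1. In the data collection section and Table 2, extend glycaemia recording to all clinically obtained values, with their times, from the last one before the first dose through 48 h after extubation.
2. Report the number of children sampled and the number of samples per arm, separately before and after extubation.
3. Compare hyperglycaemia over the whole period from first dose among children with at least one on-treatment value, alongside the comparison in all randomised children. Add a supportive analysis of events with onset before any open-label steroid or adrenaline.
4. Reconcile the clinical-samples-only rule with the persistence definition under Evaluation of Safety, stating how a child with no value or only one is classified.

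Restricting the main comparison to the time between first dose and extubation would avoid the influence of UAO and rescue, but it is not advised. With a 6 h lead, that window cannot contain hyperglycaemia lasting more than 6 h, and it leaves out the later doses.

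The cost is extra transcription of values already in the chart, plus a few lines of analysis. The pre-extubation data would still depend on clinical sampling, which is why the counts in item 2 are needed.
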